### Exclusion criteria

Patients will be excluded from the study based on the following criteria:

• Intra-articular steroid injections within 4 weeks of screening.

• Treatment with any investigational agent within 8 weeks of screening or 5 half-lives of the investigational drug (whichever is longer).

• History of drug, alcohol, or chemical abuse within 6 months prior to screening.

• Any other disease, metabolic dysfunction, physical examination finding, or clinical laboratory finding giving reasonable suspicion that might affect the interpretation of the results or render the patient at high risk from treatment complications.

• Inability to comply with study and follow-up procedures.

• Currently pregnant.

• Previous practice of Iyengar yoga within the past three months.

• Inability to speak and understand English.

According to the Power/Sample Size calculations outlined below, we will recruit 35 patients each for the IYP and control conditions. After accounting for our projected attrition rate of 20%, we estimate there will be roughly 28 treatment completers in each condition. To accommodate 56 participants during the 36-month study period, we plan to conduct 4 initial IYP groups and 4 initial control groups, with approximately 8 patients in each group.

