### Sample Size Determination and Power Analysis

A power analysis was conducted to determine the appropriate sample size. Using a pre-test post-test for randomized groups, calculating power of the interaction of treatment by time, the sample size estimate is a total sample of 54, or 27 subjects per group (at a 0.05 significance level, 80% power for a medium effect size). We calculated a medium effect size given that our recent single-arm pilot study found an effect size of .46 (Cohen's d) for the HAQ, our arthritis-specific primary outcome measure. Assuming a 20% attrition rate that is consistent with our previous yoga studies, we will recruit 35 participants for each group (total n = 70).

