For ***Hypothesis 1***: The IYP will be safe, acceptable and feasible: more than 80% of subjects will complete the training program, we will examine the frequencies of drop-outs for the IYP and control groups. We will compare attrition rates between the groups; we will also compare demographic characteristics and baseline values of functioning between those who complete the protocol and those who do not. If drop-outs are random, then the results may be considered unbiased. If drop-outs are not random, we will comment on the direction and magnitude of potential biases.

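### The plan lets results count as unbiased if drop-out is random, but the comparisons it offers for judging this cannot detect response-related drop-out and are weak with about 14 drop-outs

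*Protocol article*

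**What the plan says.** The Hypothesis 1 paragraph in Preliminary analyses plans two comparisons. The first is attrition rates between the arms. The second is to "compare demographic characteristics and baseline values of functioning between those who complete the protocol and those who do not". The next sentence draws the conclusion: "If drop-outs are random, then the results may be considered unbiased". If drop-out is not random, the authors will comment on the direction and size of possible bias. The paragraph gives no further criterion for calling drop-out random.

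The expected numbers are in the enrolment text under Exclusion criteria: "After accounting for our projected attrition rate of 20%, we estimate there will be roughly 28 treatment completers in each condition".

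Three other parts of the protocol bear on this:
- Preliminary analyses assigns missing data to multiple imputation with 20 imputations and allows auxiliary variables that predict missingness.
- Primary analyses adds an ITT analysis with last observation carried forward (LOCF), whose purpose is to confirm the completer findings.
- Exploratory variables describes a weekly monitoring form on symptoms, mood, activity and medication, completed in both arms during the 6 weeks.

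**The concern.** The sentence is a conditional, and its 'if' has to be settled by something. The only inputs offered are attrition rates and characteristics measured at or before baseline. Attrition bias in a group-by-time contrast arises when leaving depends on how a patient does after baseline, and does so differently in the two arms. Suppose yoga patients leave because they are not improving and controls leave for unrelated reasons. Baseline profiles and attrition rates can then match perfectly while the completer contrast is biased. More patients would not cure this, because the relevant variable is not in the comparison.

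The second problem is precision. With so few drop-outs, finding no difference says little even about the characteristics that are compared.

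At stake is a published statement that the yoga–control contrast is free of attrition bias. The primary outcomes are self-reported, participants know their arm, and the trial is meant to inform a larger one.

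**Working it through.** **Inputs from the protocol.** The sample-size section recruits 35 per group, 70 in all, with 20% attrition, and cites a pilot that "found an effect size of .46 (Cohen's d) for the HAQ". It states "at a 0.05 significance level, 80% power for a medium effect size" without giving sidedness; two-sided is assumed here.

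**Reproducing the plan's figures.** 35 × 0.80 = 28 completers per group, as stated. So 2 × 28 = 56 completers and 70 × 0.20 = 14 drop-outs, or 7 per arm if attrition is equal.

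**1. What the comparisons can see.** The two comparisons use the attrition rate by arm, demographics and baseline functioning. None uses a value measured after baseline, so drop-out driven by response and unrelated to baseline leaves no trace in them.

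**2. Power of a baseline comparison.** The protocol names no test. For illustration, take a two-sample t-test at two-sided 5%, with noncentrality d / √(1/n₁ + 1/n₂).
- 14 vs 56: √(1/14 + 1/56) = 0.299. For d = 0.5 the noncentrality is 0.5/0.299 = 1.67 on 68 df (critical t 1.995), so power is 38% and 62% are missed.
- At the protocol's own d = 0.46, power is 33% and 67% are missed.
- Power reaches 50% at d ≈ 0.59, is 75% at d = 0.8, and reaches 80% at d ≈ 0.85.
- Within one arm, 7 vs 28: √(1/7 + 1/28) = 0.423. For d = 0.5, power is 21% and 79% are missed.

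**3. Power of the attrition comparison, 35 vs 35** (exact binomial enumeration, two-sided 5%).

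| Attrition | Missed, chi-square | Missed, Fisher |
|---|---|---|
| 15% vs 25% | 82% | 88% |
| 20% vs 40% | 55% | 64% |
| 5% vs 35% | 7% | 13% |

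**4. What could pass unseen (illustration).** Assumptions, none from the documents: no true effect; 7 of 35 leave each arm; yoga leavers are the 7 highest on a score correlated r with poor change; control leavers are random; drop-out is unrelated to baseline. The analysis uses completers only.

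Removing the worst 20% of a normal distribution raises the mean of the rest by φ(z₀.₂)/0.8 = 0.35 SD, or 0.34 SD in simulation at n = 35. With imperfect selection the bias is about r × 0.34.

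| r | Bias, SD of change | False-positive rate (nominal 5%) | One baseline check passes |
|---|---|---|---|
| 0 | 0.00 | 5% | 95% |
| 0.5 | 0.17 | 10–11% | 95% |
| 0.8 | 0.27 | 20% | 95% |

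The pass rate is the same in every row: the check raises only its own 5% false alarms, whatever the bias. Restricting to trials that pass it leaves the false-positive rate unchanged.

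**5. Would LOCF remove it?** Someone who leaves before the post-treatment visit has baseline carried forward, so a change of zero. Under the same mechanism the yoga mean becomes (28 × 0.17 + 7 × 0)/35 = 0.14 SD for r = 0.5, and (28 × 0.27)/35 = 0.22 SD for r = 0.8. The bias is smaller but still there.

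**The case against.** **The conditional is true as written.** If drop-out really were random, completer results would be unbiased, and the sentence is hedged. A reader might infer that the protocol equates a non-significant test with random drop-out. It does not say so: it names no test, level or margin here. What stands is that the sentence follows directly on the comparisons and no other basis for the judgement is given.

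**Nothing in the analysis turns on the answer.** Imputation and the ITT analysis go ahead either way, and the paragraph concerns feasibility. That is correct. The defect lies in the statement it licenses about the results, not in a choice of model.

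**The plan has safeguards.** Weekly data after baseline would often record worsening before a patient leaves, and the imputation may use auxiliary variables. So a reader should not take 0.17–0.27 SD as the bias of the whole plan. But imputation as described assumes drop-out depends only on observed data, and LOCF assumes no change after the last visit. The planned comparisons test neither assumption, and the sentence is not conditional on either method.

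**The illustration is chosen.** One-sided selection comes from no passage, and independence from baseline builds in the 95% pass rate. Perfect selection (r = 1, about 0.34 SD and 30% false positives) is only a deterministic limit. Calling yoga the physically demanding arm would also go too far: the protocol describes a non-stressful activity with props and modified poses, although it concedes an extensive time commitment.

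**Several variables would be compared.** With five independent checks all would pass 0.95⁵ = 77% of the time. Miss rates for genuine baseline differences would also be lower than for one variable. Under the assumed mechanism, though, the extra flags are false alarms and carry no information about the bias.

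**Conclusion.** The concern holds as an unsupported inference. The comparisons offered cannot establish that drop-out is unrelated to post-baseline response, and this part rests on no numerical assumption.

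The weakness from numbers is confined to small-to-medium differences. At an assumed two-sided 5%, baseline differences up to about 0.59 SD are missed at least half the time, as is attrition of 20% vs 40%. A reader might conclude that the checks miss most differences of any size, but large ones are usually found: 0.8 SD about 75% of the time, and 5% vs 35% attrition about 90%.

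The bias figures show what an all-clear could conceal in a completer analysis under an assumed mechanism. They do not predict this trial's bias. The point deserves correction because completers carry the main findings and the ITT analysis is there to confirm them.

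**What to change.** 1. Delete the sentence that lets results be considered unbiased if drop-outs are random.
2. Keep the attrition and completer/drop-out comparisons as description, with confidence intervals, and state that similar baseline profiles do not establish random drop-out.
3. Base any statement about attrition bias on a sensitivity analysis of the group-by-time effect. Use the 20 imputations already planned, with the weekly monitoring data as auxiliary variables. Shift the imputed values of yoga drop-outs by increasing amounts and report the shift at which the conclusion changes.

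The cost is a wording change and one extra analysis run. Sample size, conduct and data collection stay as they are. The authors lose the option of calling the results unbiased on the strength of these comparisons.

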### Primary analyses

To test ***Hypothesis 2***: Participants in the IYP will demonstrate significantly greater improvement in HRQOL and functioning compared to controls. The primary outcomes include the SF-36, PDI and the HAQ. Two sets of analyses will be conducted. The first set of analyses will compare the initial yoga and control groups immediately after the IYP and control phase, respectively. Separate mixed group (yoga vs. control) by time (baseline vs. post-treatment/post-control) repeated measure analysis of variance (ANOVA) will be conducted on the primary outcomes, or the non-parametric equivalent (Friedman procedure), in the event the assumptions for parametric analyses are not met. We will use the Tukey-Fisher criteria for post hoc mean/median comparisons under the ANOVA or Friedman model. Consistent with ***Hypothesis 2***, we expect a group by time interaction wherein the yoga group will report improved functioning from baseline to post-treatment compared to the control group. The second set of analyses will assess maintenance of treatment gains during the follow-up period. If yoga and control groups do not differ significantly on SF-36, PDI and HAQ scores at baseline, then data from the two groups will be combined in order to maximize power. If groups differ at baseline, each group will be analyzed separately. Changes in SF-36, PDI and HAQ scores across baseline, post-treatment and follow-up will be evaluated using separate within-group repeated measures ANOVAs; Friedman's procedure will be used if parametric assumptions are not met. Consistent with ***Hypothesis 2***, we expect significant improvements in functioning scores from baseline to post-treatment, persisting at follow-up.

We will also conduct an ***intent-to-treat (ITT) analysis***on primary outcomes to confirm our findings in completers by including all participants who enrolled in the study, using the last observation carry forward approach. Participants who drop out will be included in the analysis by utilizing outcome scores before attrition.

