### Preliminary analyses

Once the data set has been cleaned and examined for skewness and missing data, exploratory data analyses will be conducted using univariate methods to describe the variables of interest and bivariate techniques to characterize their interrelationships within our sample. Continuous variables will be summarized over time in each group using means and medians and we will also report their range, interquartile range and standard deviations. Cross tabulated frequencies will be given for all discrete variables by group and time. Results from these descriptive analyses will be used to guide the primary analyses by providing information about potential problem measures (e.g., heavily skewed distributions) or problematic variable relationships (e.g., highly correlated predictors) and will help determine if transformations of some outcomes are possible in order to use parametric methods. We will test for baseline between-group differences in the outcome measures. Any variables found to vary significantly by group will be included as covariates in primary and secondary analyses. This will also serve to verify that the randomization was successful.

Missing data will be handled using multiple imputation [74] using the SAS routines PROC MI (20 imputations) and PROC MIANALYZE (to combine estimates). The imputation process is fostered by including additional variables (not part of the intended analytic model) that are highly correlated with variables that have missing data or that are associated with the probability that those variables have missing data. Such covariates (used in imputation only) will vary from analysis to analysis and their viability will be evaluated by preliminary analysis (e.g., zero-order correlations with variables with missing data) and their impact on the imputation model (e.g., change in standard errors of imputed variables). Multiple imputation has been shown to perform well with small samples [74].

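### The non-parametric fallback for the primary group-by-time test is Friedman's procedure, which has no group factor and cannot test Hypothesis 2; separately, always adjusting for baseline would gain some power at no cost

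*Protocol article*

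**What the plan says.** Primary analyses (protocol article), first set, names the parametric model: "Separate mixed group (yoga vs. control) by time (baseline vs. post-treatment/post-control) repeated measure analysis of variance (ANOVA) will be conducted on the primary outcomes". The substitute for that model is then given as "or the non-parametric equivalent (Friedman procedure), in the event the assumptions for parametric analyses are not met". The effect sought is stated: "we expect a group by time interaction wherein the yoga group will report improved functioning from baseline to post-treatment compared to the control group". The section then plans post hoc comparisons under either the ANOVA or the Friedman model. Secondary analyses applies the same methods to the secondary outcomes.

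Preliminary analyses says that transformation will be considered so that parametric methods can be used. The fallback is therefore second-line. No other non-parametric test is named.

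On baseline, Preliminary analyses says "We will test for baseline between-group differences in the outcome measures" and "Any variables found to vary significantly by group will be included as covariates in primary and secondary analyses", adding "This will also serve to verify that the randomization was successful".

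The second set of primary analyses is within-group, across baseline, post-treatment and follow-up, and again names Friedman as the fallback.

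**The concern.** Hypothesis 2 is a comparison of randomised arms. Friedman's procedure ranks each person's own scores across times and asks whether scores shift over time. It contains no term for arm. If the fallback were used as written, the p-value reported for a primary outcome would answer a different question. Improvement shared by both arms could be read as a yoga effect, and a real difference between arms could go unseen.

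The baseline rule is a lesser matter. It ties adjustment to a significance test, so under randomisation a given outcome's baseline becomes a covariate in only about 1 trial in 20. At stake there is precision, in a trial that expects about 56 completers.

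**Working it through.** **Inputs.** From the article: 35 recruited per arm and 20% attrition, so 35 × 0.8 = 28 completers per arm, which agrees with its own figure; alpha 0.05 (taken as two-sided); pilot effect d = 0.46 for the HAQ, from a single-arm study. Assumed, because the article gives none: the baseline-to-post correlation r (0.5, 0.7, 0.8) and the size of any improvement common to both arms (0 to 0.46 SD of change). All calculations use normal, complete data unless stated.

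**Step 1: what Friedman becomes with two times.** Let K be the number of n people who improve, with no ties. The statistic reduces to (2K − n)²/n on 1 df, which is a sign test. Arm does not appear in it.
- Pooled, n = 56: reject when |2K − 56| > √(3.841 × 56) = 14.67, so K ≥ 36 or K ≤ 20.
- One arm, n = 28: reject when |2K − 28| > √(3.841 × 28) = 10.37, so K ≥ 20 or K ≤ 8.

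**Step 2: no yoga effect, both arms improve by δ SD of change.** Each person improves with probability Φ(δ). The rejection probabilities are exact binomial sums. If the test is run by arm, the chance that yoga is significant and control is not is P(1 − P), where P is the one-arm rejection probability.

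| δ | Φ(δ) | Pooled Friedman rejects | P (one arm) | Yoga significant, control not |
|---|---|---|---|---|
| 0 | 0.500 | 4% | 0.036 | 3% |
| 0.1 | 0.540 | 8% | 0.052 | 5% |
| 0.2 | 0.579 | 21% | 0.105 | 9% |
| 0.3 | 0.618 | 41% | 0.198 | 16% |
| 0.46 | 0.677 | 76% | 0.423 | 24% |

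**Step 3: a true interaction with no average time trend.** One arm improves and the other worsens by 0.46 SD of change. The expected number improving is 28 × 0.677 + 28 × 0.323 = 28 of 56, exactly the null value, and pooled Friedman rejects in 3%. A two-sample t-test on change has noncentrality 0.92 × √(28/2) = 3.44 against a critical value of about 2.0, giving power of about 92%.

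**Step 4: does an arm-comparing rank method behave?** With simulated skewed, floored 0–3 scores, 28 per arm, a shared shift of 0.46 on the underlying scale and no arm effect, Friedman rejects in 79% (r = 0.5) and 94% (r = 0.7). Rank ANCOVA rejects in 5.2% and 4.8%, and the ordinary change-score test in 5.0% and 4.8%.

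**Step 5: the covariate rule.** The two-time interaction test is a t-test on change, with SD √(2(1 − r)). ANCOVA has residual SD √(1 − r²). The rule was simulated as the change-score test unless the baseline difference has p < 0.05, and ANCOVA otherwise (40,000 data sets). The true effect is 0.46 **raw** SD, a different scale from Step 2; the two coincide only at r = 0.5, where the SD of change is 1.

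| r | SD of change | ANCOVA SD | Power, stated rule | Power, ANCOVA always |
|---|---|---|---|---|
| 0.5 | 1.000 | 0.866 | 40% | 49% |
| 0.7 | 0.775 | 0.714 | 59% | 64% |
| 0.8 | 0.632 | 0.600 | 76% | 80% |

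Before rounding, the gains are 9.8, 5.7 and 3.3 points. With no effect, the rule rejects in 4.2 to 4.8% and ANCOVA in about 5%.

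**The case against.** The fallback may never be used. Transformation comes first, and skewed raw scores need not upset the ANOVA: Step 4 shows the change-score test holding its level with skewed, floored scores. Both points stand. They limit how often the error would bite, but they do not turn Friedman into a test of arms.

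The 76% gives usual-care controls the full 0.46 seen in a single-arm yoga pilot, and nothing in the article supports so large a control improvement. That also stands, which is why the range matters. A reader might infer a false-positive rate of 76% for this trial; the article supports no such statement.

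A reader might also infer that the covariate rule inflates type I error, leaves the baseline unused, or does harm by entering it twice. None of these holds. Step 5 shows no inflation. A change score uses the baseline by subtracting it. ANCOVA of change on baseline gives the same arm test as ANCOVA of the post score on baseline, so when the rule triggers it can deliver the very model recommended here. What remains is efficiency, and at r near 0.8, one assumption under which the article's 27 per group can be reached, the gain is only about 3 points.

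On checking randomisation, the Randomization section allocates before baseline assessment. A baseline difference could therefore reflect knowledge of allocation as well as chance, and the test cannot tell the two apart.

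**Conclusion.** The fallback is wrong as written for the first set of primary analyses, and for the secondary outcomes that inherit it. This follows from the form of the test and needs no assumption. How misleading it would be depends on the improvement common to both arms and on whether it is run pooled or by arm: with no yoga effect, from 4% to 76% pooled, or 3% to 24% as a yoga-only significant result, over 0 to 0.46 SD of change. With opposite changes of 0.46 it detects the difference in 3%.

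The error does not reach the mixed ANOVA, which is valid when its assumptions hold, or Friedman in the three-time within-group analyses.

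The baseline-covariate rule is a separate efficiency point, worth about 3 to 10 points of power for assumed r from 0.8 down to 0.5 at a true effect of 0.46 raw SD.

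**What to change.** 1. For each outcome, make the primary model an ANCOVA of the post-treatment score on arm and that outcome's baseline score, always included.
2. Delete the rule that adds covariates according to baseline significance, and the claim that the baseline test verifies randomisation.
3. Name one fallback that compares the arms, with a trigger fixed in advance. Rank ANCOVA suits the plan: rank within each of the 20 imputed data sets, fit the model, and combine the arm estimate and standard error with PROC MIANALYZE. A permutation or rank-sum p-value has no stated pooling route in this plan.
4. Keep Friedman for the within-group analyses only, and make the matching change for the secondary outcomes.
5. State that ANCOVA, like the change score, assumes that knowing the allocation did not shift the self-reported baseline, since allocation comes first.

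The cost is wording; no new data are needed. The fix leaves untouched the other use of baseline significance, which decides whether the arms are pooled for the follow-up analyses; that rule needs its own decision.

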### Secondary analyses

To test ***Hypothesis 3***: Participants in the IYP will report significantly less pain, improved joint count, and mood compared to controls. The same methods used for the primary analyses will be used for the secondary analyses on pain intensity (averaged across the weekly NRS ratings taken during the initial 6-week IYP/control period) and mood. Consistent with ***Hypothesis 3***, we expect that the yoga group will evidence greater improvements on these measures over the 6-week treatment period relative to controls. We will also conduct similar within-group repeated measures analysis, as described in the primary analyses above, to examine changes in the secondary measures from baseline to post-treatment and follow-up. Consistent with ***Hypothesis 3***, we also expect that benefits will be maintained over the two-month follow-up period.

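### Whether the immediate and delayed yoga groups are pooled for the maintenance analysis is decided by a baseline significance test, which is the wrong criterion for combining their courses over time

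*Protocol article*

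**What the plan says.** The protocol's Primary analyses section describes two sets of analyses for Hypothesis 2. The first is the randomised group-by-time comparison from baseline to the end of the yoga or control phase. This point concerns the second: "The second set of analyses will assess maintenance of treatment gains during the follow-up period". By then the wait-list group has also taken the yoga course, so there are two cohorts, immediate and delayed.

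The rule for combining them is explicit. If the yoga and control "groups do not differ significantly on SF-36, PDI and HAQ scores at baseline, then data from the two groups will be combined", with maximum power given as the reason. The other branch reads: "If groups differ at baseline, each group will be analyzed separately". Changes "across baseline, post-treatment and follow-up will be evaluated using separate within-group repeated measures ANOVAs". No comparison of the two cohorts' courses is named for this set.

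The Secondary analyses section adds: "We will also conduct similar within-group repeated measures analysis, as described in the primary analyses above". It does not repeat the pooling rule, so carrying the rule over to the secondary outcomes is a natural reading but an inference.

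Three other places bear on the point:
- The Design section re-assesses wait-list participants after 6 weeks, and only those still eligible start yoga.
- The Design and Randomization sections place allocation before the baseline assessments.
- The Preliminary analyses section responds to a significant baseline difference in another way, by adding the variable as a covariate.

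**The concern.** A within-subject analysis over three times estimates change. Combining two cohorts is informative when their changes are similar. The rule tests baseline means instead, and a difference in baseline means does not by itself bias a within-subject time effect. The feature that would make a pooled result misleading, a different course in the delayed cohort, is not what decides. Such a difference is plausible, because that cohort has waited 6 weeks and been re-screened.

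The rule can therefore err in two ways. It can split the analysis when nothing is wrong, losing the power that pooling was meant to secure. It can also pool cohorts that respond differently. If the immediate cohort gained 0.5 SD and an equally large delayed cohort gained nothing, the pooled change would be (0.5 + 0)/2 = 0.25 SD, which describes neither.

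Benefit at two months is part of Hypotheses 2 and 3, and this is the analysis that addresses it.

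**Working it through.** **Inputs from the protocol.** 35 recruited per group and 20% attrition give 35 × 0.8 = 28 completers per group, 56 in all, which matches the Exclusion criteria section. The Sample Size section gives "at a 0.05 significance level, 80% power for a medium effect size" and "our recent single-arm pilot study found an effect size of .46 (Cohen's d) for the HAQ". The Primary outcomes section describes the SF-36 as having eight scales, so the baseline rule covers 3 tests (one per instrument) or 8 + 1 + 1 = 10.

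**Assumptions.** Baseline tests are two-sided at 0.05. Correlations among the scores are 0.3 to 0.7. Pre-post correlation, where needed, is varied.

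**The plan's own figure.** The protocol gives no operating figure for the pooling rule. Its sample size statement is that "the sample size estimate is a total sample of 54, or 27 subjects per group". For a 2 × 2 group-by-time interaction, noncentrality is f² × N × 2/(1 − ρ). N = 54 results from f = 0.25 with ρ = 0.2 (power 0.813), or from f = 0.23 with ρ = 0.3 (power 0.801). The correlation is not stated, so 54 is attainable but cannot be confirmed. Nothing below depends on it.

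**1. Does non-significance show similarity?** For a two-sample t-test with 28 per group and a true gap of 0.5 SD, noncentrality is 0.5 × √(28/2) = 1.87 on 54 df, and power is 45%. A gap of that size is missed 55% of the time on any one score.

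**2. How often does the rule split groups that are truly alike at baseline?** For independent tests, the chance of at least one significant result is 1 − 0.95^k. For correlated scores it was simulated at 28 per group; results at 35 were nearly the same.

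| Tests | Independent | Correlation 0.3 | 0.5 | 0.7 |
|---|---|---|---|---|
| 3 | 14.3% | about 14% | about 12-13% | about 11% |
| 10 | 40.1% | about 35% | about 29% | about 22% |

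The text does not say whether one significant score splits every analysis or only its own. If only its own, the rate is 5% per score.

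**3. What does a split cost?** For a two-sided paired t-test, noncentrality is dz × √n. The protocol does not say what SD standardises the pilot's 0.46. If it is already a paired standardised change, dz = 0.46. If it uses the baseline SD, with equal SDs at both times, dz = 0.46/√(2(1 − ρ)).

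| Reading of 0.46 | dz | Power, n = 56 | Power, n = 28 |
|---|---|---|---|
| Paired change | 0.46 | 92% | 65% |
| Baseline SD, ρ = 0.3 | 0.46/1.183 = 0.389 | 82% | 51% |
| Baseline SD, ρ = 0.7 | 0.46/0.775 = 0.594 | 99% | 86% |

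The 95% confidence interval widens by (2.052/√28)/(2.004/√56) = 1.45. These figures are for change from baseline to post-treatment.

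**4. Does the rule respond to a difference in course?** With equal baseline means and 28 per group, courses differing by 0, 0.5 or 1.0 SD were simulated. The chance of pooling on one test stayed at 95% each time, because a difference in later change does not alter the baseline test. A direct cohort-by-time test on the same data was significant in 5%, 45-66% and 96-99.7% of runs (pre-post correlation 0.5-0.7).

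**The case against.** The strongest objection is that a significant baseline difference here need not be a chance event. Allocation precedes the baseline assessments, SF-36, PDI and HAQ are self-reported, and only the physician doing the joint count is described as unaware of assignment. Participants who knew their group could answer differently. The text also leaves open whether the delayed cohort's baseline is study entry or the assessment just before yoga. Under the second reading, waiting, drop-out and re-screening could shift scores. This stands: a reader might infer that every split is a false alarm, and the protocol does not support that. The rates in step 2 apply only if the groups are truly alike at baseline. Neither reading makes a baseline test a valid criterion for pooling change.

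Second, a reader might infer that the baseline test carries no information at all about change. That holds when change is unrelated to baseline. If the two correlate at −0.5 (assumed) and the cohorts do not truly differ, observed changes differ significantly in 18% of trials where the baseline test is significant, against 4% where it is not. It is then a weak signal, partly of regression to the mean.

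Third, a split discards nobody and pooling is the likelier outcome. This also stands: the sample is not simply halved.

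Fourth, the Preliminary analyses section summarises outcomes over time by group, so divergent courses would be visible, and a cohort-by-time test has only moderate power at this size. Both are true. They favour always estimating the interaction with its interval, and give no reason to keep the baseline test.

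Last, this is an uncontrolled within-group analysis in a pilot study, which limits the seriousness of the point.

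**Conclusion.** The point holds in a limited form. The protocol fixes a pooling rule that tests baseline means when the relevant question is similarity of change, and it reads non-significance at about 28 per group as licence to combine.

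If the groups are alike at baseline, a needless split occurs in about 11-14% of trials with three scores and about 22-35% with ten, at assumed correlations of 0.3-0.7. The ten-test figure requires separate testing of the SF-36 scales, which the protocol does not state. When a split occurs, power falls from 92% to 65% on the paired reading of 0.46, and from 82% to 51% or from 99% to 86% on the baseline-SD readings. In the other direction, cohorts with different courses but equal baseline means are pooled as often as cohorts that respond alike.

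A reader might infer that the trial's main treatment comparison is compromised. It is not: the randomised comparison from baseline to post-treatment does not use this rule. The consequence is confined to the maintenance analysis and, if the rule carries over, to the similar secondary analyses. The change is worth making because it is nearly free and this analysis addresses the two-month part of Hypotheses 2 and 3.

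**What to change.** Remove the baseline-significance rule from the Primary analyses section. For each primary outcome, always fit one repeated-measures model to both cohorts, with cohort (immediate or delayed), time and cohort-by-time. Define baseline as each participant's assessment before starting yoga; for the delayed cohort this is the assessment at the end of the control phase. Report the cohort-averaged change as the main follow-up estimate. Beside it, give the two cohort-specific changes and the cohort-by-time estimate with its confidence interval, and do not let the significance of that interaction decide whether to pool. State that the same applies to the similar within-group analyses in the Secondary analyses section.

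This uses assessments already planned. The cost is a change of wording and a few degrees of freedom for the cohort and interaction terms.
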